## Abstract

**Background:**

Every year, more than 5500 healthy people in the United States donate a kidney for the medical benefit of another person. The Organ Procurement and Transplantation Network (OPTN) requires transplant hospitals to monitor living kidney donors (LKDs) for 2 years postdonation. However, the majority (115/202, 57%) of transplant hospitals in the United States continue to fail to meet nationally mandated requirements for LKD follow-up. A novel method for collecting LKD follow-up is needed to ease both the transplant hospital-level and patient-level burden. We built mKidney—a mobile health (mHealth) system designed specifically to facilitate the collection and reporting of OPTN-required LKD follow-up data. The mKidney mobile app was developed on the basis of input elicited from LKDs, transplant providers, and thought leaders.

**Objective:**

The primary objective of this study is to evaluate the impact of the mKidney smartphone app on LKD follow-up rates.

**Methods:**

We will conduct a two-arm randomized controlled trial (RCT) with LKDs who undergo LKD transplantation at Methodist Specialty and Transplant Hospital in San Antonio, Texas. Eligible participants will be recruited in-person by a study team member at their 1-week postdonation clinical visit and randomly assigned to the intervention or control arm (1:1). Participants in the intervention arm will receive the mHealth intervention (mKidney), and participants in the control arm will receive the current standard of follow-up care. Our primary outcome will be policy-defined complete (all components addressed) and timely (60 days before or after the expected visit date) submission of LKD follow-up data at required 6-month, 1-year, and 2-year visits. Our secondary outcome will be hospital-level compliance with OPTN reporting requirements at each visit. Data analysis will follow the intention-to-treat principle. Additionally, we will collect quantitative and qualitative process data regarding the implementation of the mKidney system.

**Results:**

We began recruitment for this RCT in May 2018. We plan to enroll 400 LKDs over 2 years and follow participants for the 2-year mandated follow-up period.

**Conclusions:**

This pilot RCT will evaluate the impact of the mKidney system on rates of LKD and hospital compliance with OPTN-mandated LKD follow-up at a large LKD transplant hospital. It will provide valuable information on strategies for implementing such a system in a clinical setting and inform effect sizes for future RCT sample size calculations.

**International Registered Report Identifier (IRRID):**

DERR1-10.2196/11000

## Introduction

### Need for Living Donor Kidney Transplantation

Almost 100,000 patients with end-stage renal disease (ESRD) are currently on the waitlist for a deceased donor kidney transplant (DDKT) in the United States. An additional 30,000 are added to the waitlist each year. In 2017, only 14,038 received a DDKT. Most patients who are listed for a kidney transplant today (who do not have a living donor) will have to wait 3-7 years to get an organ offer. Live donor kidney transplantation (LDKT) offers patients with ESRD a timely and therapeutic modality that has superior outcomes to DDKT and dialysis [1]. LDKT has been recognized and promoted as the best treatment option for patients with kidney failure by the American Society of Transplantation Living Donor Community of Practice in a consensus statement [2].

### Sequelae of Living Kidney Donation

Living kidney donors (LKDs) experience 50% nephron loss (ie, one kidney) following donor nephrectomy, with the immediate consequence of 25%-40% loss of renal reserve as measured by the glomerular filtration rate (GFR). The health risks of this loss of GFR at nephrectomy appear to be minimal for most LKDs, with an estimated lifetime risk of ESRD of 90 per 10,000 LKDs [3-5]. However, further GFR loss might be consequential for some LKDs in the long term, especially in the event of *de novo* disease [5,6]. Diabetes mellitus (DM), hypertension (HTN), and glomerulonephritis account for over 60% of documented cases of ESRD in the LKD population [7].

Moreover, there are racial disparities in postdonation outcomes. In a national study linking Organ Procurement and Transplantation Network/United Network for Organ Sharing (OPTN/UNOS) registry data with administrative data of a private US health insurer, Lentine et al found that African American LKDs have a 1.5-fold higher risk of HTN, a 2.3-fold higher risk of DM, and a 2.3-fold higher risk of chronic kidney disease (CKD) compared with Caucasian LKDs at 7 years postdonation [8]. Using the same linkage, Lentine et al found that this disparity persisted across age, sex, and biological relationship to the recipient. The adjusted incidence of any renal diagnosis was higher among African American LKDs compared with Caucasian LKDs (14.9% vs 9.0%; adjusted hazard ratio [aHR] 1.72; *P*=.002), including CKD (12.6% vs 5.5%; aHR 2.32), proteinuria (5.7% vs 2.5%; aHR 2.27), and nephrotic syndrome (1.3% vs 0.1%; aHR 15.7) [9]. Within 15 years, African American LKDs have a higher absolute risk of ESRD (74.7 cases per 10,000 LKDs) than Caucasian (22.7 per 10,000) or Hispanic LKDs (32.6 per 10,000) [4]. While the overall risk of developing a renal disease is low [4], follow-up and self-care management are important.

### Importance of Living Kidney Donor Follow-Up to Reduce Progression to Late-Stage Renal Disease

Long before *de novo* diseases cause CKD and ESRD, they manifest as hyperglycemia, elevated blood pressure, proteinuria, and hematuria. Routine laboratory tests can screen for these subclinical entities. Appropriate LKD follow-up might present an opportunity for early detection and control of DM, HTN, glomerulonephritis, and CKD, thus slowing CKD or ESRD progression. Routine screening is especially important for young donors who face many decades with reduced renal reserve and, thus, a higher lifetime risk of ESRD.

### Current Landscape of Living Kidney Donor Follow-Up

OPTN/UNOS has collected postdonation follow-up data on LKDs since 1999. However, LKD follow-up has remained consistently poor. This prompted a national policy that began requiring centers to collect these data beginning in 2013 [10,11]. OPTN/UNOS now requires transplant hospitals to collect and submit clinical data (the presence of HTN, diabetes, dialysis, kidney-related complications, recent hospitalizations, medical insurance status, income, and vital status) for 80% and laboratory data (serum creatinine and urine protein) for 70% of LKDs for 2 years postdonation (Multimedia Appendix 1). Transplant hospitals are required to collect these data from each LKD within a 120-day period (60 days before or after the 6-month, 1-year, or 2-year postdonation date) for each follow-up visit [10]. Implementation of this requirement has shown limited improvement. In a national study, we found that only 43% (87/202) of transplant hospitals met OPTN/UNOS-mandated 6-month, 1-year, and 2-year thresholds for LKDs who donated in 2013 [12]. In the face of barriers, such as cost, LKD inconvenience, and the burden of data collection [13,14], transplant hospitals lack the tools to improve LKD engagement.

### Appropriate Living Kidney Donor Follow-Up Might Improve Our Ability to Understand Long-Term Sequelae of Donation

Given the limitations of the current system of LKD follow-up, alternative approaches are of utmost urgency to enable the medical community to uphold its obligation to care for living organ donors. To date, knowledge of postoperative health outcomes has largely been limited to perioperative mortality, long-term survival, and ESRD risk prediction, accounting for differences among racial and ethnic minorities [8,15-19]. Because of the lack of national follow-up and long-term data, inferences on long-term donor morbidity have been limited primarily to risks of cardiovascular disease, CKD, and ESRD [5,20,21]. In addition, only limited pilot data are available on the effect of donation on the pathophysiology of cardiovascular disease; hence, more research is needed to better define the effects of donation on cardiovascular disease surrogates and clinical events [22].

### Benefits of mHealth Technology to Patients and Providers

As mobile phone use has changed the way providers communicate with patients and each other, there is a need to develop the science of mobile health (mHealth) [23,24]. mHealth apps designed for smartphones are perceived to offer considerable potential as tools to engage patients in chronic disease management [25]. mHealth technologies have been implemented in several chronic disease settings with promising results. Users of an mHealth system to promote self-management among patients with type-2 diabetes (mDAWN) experienced improved disease biomarkers and decreased health distress after using the app for a 3-month period [26]. Delivery of an mHealth intervention for the prevention of weight gain (TXT2BFiT) resulted in modest but sustained weight loss after 9 months [27]. Furthermore, mHealth technologies have shown promise in facilitating behavioral interventions to reduce cardiovascular risk factors such as smoking, physical inactivity, and suboptimal nutrition [28].

### Benefits of Patient Engagement

Growing evidence suggests that health care is more efficient and effective when patients are actively engaged in their treatment [29]. Engaged patients collaborate with their providers, are better treated with respect and dignity, receive information related to their care, and are involved in decision making [30]. LKDs who are better engaged and informed may be able to keep better track of their postdonation health and may benefit from being able to visualize and summarize their health information, receive guidance on preventive care, and communicate with health care providers and the transplant system.

### Preliminary Data

In formative research conducted at the Johns Hopkins Hospital, 95 of 100 LKDs reported owning a smartphone [31], which is consistent with Pew Research Center findings that 92% of adults in the United States owned a mobile phone in 2015 [32]. Among participants, 80% (80/100) thought that mHealth technology would be useful in completing follow-up [31]. A pilot study of 69 LKDs found that engagement through short message service (SMS) text messages exceeded 80% at 2 years postdonation, compared with only 20% using traditional follow-up engagement strategies (ie, telephone; electronic medical record, EMR; or patient portal). Most LKDs (97%) selected electronic communication (email or SMS text message) as their preferred method of postdonation communication with the study team, with no significant differences by sex or race [33]. These findings demonstrate the feasibility of using electronic communications, like mHealth, to improve existing methods of postdonation communication with LKDs.

### Innovation

#### Design and Development of a New Technology

An effective method of follow-up communication with LKDs that does not place an undue burden on either patients or providers, allows for the monitoring and tracking of surgical recovery milestones, and can detect the development of *de novo* kidney disease to intervene when possible is needed. We designed an mHealth platform to capitalize on the available computing power and technologies that can transform the reach of medical care and research [34].

#### Novel Approach to Improve a Health System Failure

SMS text messages, emails, and mHealth are promising new approaches to rectify the striking gap in regular postdonation medical care for LKDs. mHealth interventions have been evaluated in clinical trials for self-management support, weight management, and prevention and management of cardiovascular disease and diabetes in other populations [26-28,35-38]. An mHealth system to engage LKDs in postdonation follow-up care might improve transplant hospitals’ ability to achieve compliance with OPTN/UNOS-mandated reporting requirements and provide a link to critical preventive care for LKDs.

#### Benefit and Innovation of mHealth for Living Kidney Donor Follow-Up

Despite the recent proliferation of mHealth technologies, few are currently used in research studies [39]. The National Institutes of Health (NIH) strategic plan supports contributing to the mHealth evidence base because everyone can use this technology [40]. With donors from the UNOS Living Donor Committee and among informal conversations with LKDs on Facebook, we identified the following 5 primary benefits to an mHealth system for LKD engagement and follow-up: (1) *portability*: mHealth goes beyond point-of-care clinical diagnostics, thus following the LKD past transplant hospital visits; (2) *scalability*: mHealth platforms have been shown to be economical to scale [41], and with no current mechanism for reimbursement for required follow-up, transplant hospitals absorb the cost; (3) *rich data input through continuous data sampling*: devices and wearables are meant to integrate with daily functions making data collection convenient, which could make LKD follow-up automatic and seamless; (4) *personalization capacity*, and (5) *real-time data and feedback with the ability for automated analyses*. An mHealth system could provide LKDs with an opportunity to medically engage with the hospital where they donated a kidney, ask for medical record review, and have a built-in system to alert primary care health care providers when laboratory tests or blood pressure measurements become worrisome. Novel applications of inexpensive and automated electronic communication technologies, such as mHealth, could enhance patient follow-up and be applied to other patient populations. In an environment of spiraling health care costs where paperwork is administratively expensive and burdensome, this technology could find broad application.

**Figure 1 figure1:**
[figure not shown]
Adapted conceptual framework for living kidney donor follow-up.

### Overview and Theoretical Framework

This research is based on the Donabedian 3-factor conceptual framework of care quality, adapted to LKD follow-up (Figure 1) [42,43]. In the adapted conceptual framework, structures of care include the national organ transplant system and the transplant hospitals performing the living donor transplant surgery, which are responsible for reporting follow-up to OPTN/UNOS. Processes of care include LKD follow-up care that takes place both internal and external to the transplant hospital responsible for reporting. Outcomes include short-term (2-year) and long-term (>2-year) follow-up and vary in measures based on policy requirements and principles of prevention. The development of our mHealth system for LKD engagement and follow-up care sought to address all aspects of this framework.

### Objective

This study aims to pilot-test an mHealth system (mKidney) and design a future large-scale multicenter randomized controlled trial (RCT) of this intervention. We will recruit 400 participants (200 per year for 2 years) to pilot-test the intervention. We will compare rates of follow-up between LKDs in the intervention (mKidney system) and control arms (standard of care) at 6, 12, and 24 months to help estimate potential effect sizes of the intervention (to inform subsequent RCT design and power calculations).

## Methods

### Study Design

We are conducting an exploratory pilot RCT with parallel-group design to evaluate the impact of the mKidney system on rates of postdonation follow-up among LKDs, in preparation for a fully powered clinical trial (NCT03400085). Participants will be randomized to the intervention (mKidney system) or control arm (standard of care) and will be followed for the mandated 2-year LKD follow-up period (Figure 2).

### Study Population

We plan to enroll 400 LKDs who have donated a kidney at Methodist Specialty and Transplant Hospital in San Antonio, Texas, during the study period. LKDs randomized to the intervention arm (approximate n=200) will receive the mKidney system, whereas LKDs randomized to the control arm (approximate n=200) will receive the current standard of follow-up care.

### Inclusion and Exclusion Criteria

For the pilot RCT, LKDs who have donated a kidney at the Methodist Specialty and Transplant Hospital during the study period will be eligible for study participation. We will exclude LKDs who do not speak English or own a smartphone device; by national policy, all donors are ≥18 years of age.

### mKidney System Description

The mKidney system includes 2 components—an LKD-facing smartphone app and a transplant provider-facing Web portal. Using the Health Insurance Portability and Accountability Act (HIPAA)-compliant mKidney app, LKDs can enter their responses to required questionnaires, record lab values, and submit a photo of their lab work at each 6-month, 1-year, and 2-year follow-up time point. The questionnaire for each follow-up time point will become available at the beginning of the 120-day submission period (Multimedia Appendix 1). LKDs will receive an automated SMS text message, email, and push notifications throughout the open submission period to prompt follow-up completion. If needed, transplant providers may contact LKDs using traditional engagement strategies (eg, telephone and EMR patient portal) in addition to automated mKidney app notifications. In addition, LKDs can access Web resources through the mKidney app, including the transplant hospital website and locations of laboratory testing sites. Using the secure, HIPAA-compliant mKidney Web portal, transplant providers can monitor patients’ compliance with follow-up, log additional contact attempts, view questionnaire responses, and export data for reporting purposes.

### Study Procedure

LKDs will undergo consent and randomization at their medically required 1-week postdonation clinical visit. Study personnel who have undergone Human Subjects Training will use a written consent form to document consent (Multimedia Appendix 2). Surgeon and clinician members of the study team will not participate in recruitment activities to avoid the potential for coercion and appearance of a conflict of interest. Paradata will be collected on the number of acceptances, eligible enrollments, and refusals.

**Figure 2 figure2:**
[figure not shown]
Schematic of the study design. LKD: living kidney donor.

We will assign participants either to the intervention (mKidney system) or the control arm (standard of care) using block randomization with block sizes ranging from 2 to 8. Block randomization will improve the probability of balanced groups over the course of the study. A statistician on the Johns Hopkins study team, blind to group allocations, will use this method to generate a list of sequential group assignments using Stata 15 for Linux (StataCorp Inc). The list will be used to create sequentially numbered, sealed envelopes that will be used to allocate consenting participants to the control or intervention arms of our study. Each patient will have a 50% chance of being assigned to the intervention arm of the study. Patients, health care workers on the study team, and study team members responsible for data collection and analysis will be aware of which arm participants are randomized to. Therefore, this study will not be blinded to providers, patients, or study personnel.

Study personnel will assist participants assigned to the mHealth intervention arm with downloading the mKidney app and explain its functioning. After enrollment in the study, participants in the intervention arm will receive notifications and have the ability to complete a questionnaire documenting their remote standard-of-care visit and enter the required laboratory values at 6 months, 1 year, and 2 years postdonation using the mKidney app. Participants in the control arm will be instructed to complete the required follow-up as is standard of care but will not use the mKidney app to do so (Figure 2).

The primary outcome of interest will be the rate of policy-defined complete (all components addressed) and timely (60 days before or after the expected visit date) submission of data at all 6-month, 1-year, and 2-year follow-up visits, compared between study arms. The secondary outcome will be the transplant hospital-level compliance with OPTN reporting requirements at each visit. Outcomes will be assessed independently for each follow-up time point and as a composite outcome over the study period, as well as will be compared between study arms following the intention-to-treat principle. To understand logistical or demographic barriers to implementation, we will also collect process data and utilize routinely collected data on LKDs in the study. These data include age, sex, race, ethnicity, and educational level of LKDs.

There will not be study-specific efforts to retain participants or promote the use of the mKidney app for LKD follow-up data submission, as this would be a form of intervention that might impact outcomes. However, transplant providers at Methodist Specialty and Transplant Hospital may contact LKDs for obtaining complete and timely LKD follow-up data to comply with nationally mandated follow-up requirements. Participants may withdraw from the RCT at any time without penalty. Withdrawal from the RCT would not preclude participants from obtaining regular medical care or follow-up care related to their kidney donation. If participants choose to withdraw, the study team will use the data collected prior to withdrawal and mark the remaining data as censored. Other than interventions that might impact the rates of LKD follow-up compliance, no concomitant care or interventions will be prohibited during the trial.

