### Sample Size and Power Calculation

If we recruit a total of 400 LKDs over a 2-year period and the proportion of control arm LKDs with compliant follow-up is 50%, we will have 80% power to detect a difference of 13.8% and 90% power to detect a difference of 15.9% (Table 1). If the projected follow-up rate of donors in the intervention arm is 67% (the minimum threshold for policy compliance), this study will have 79% power to detect a difference. If the follow-up rate in the intervention arm is 70%, this study will have 95% power to detect a difference (Figure 3). There is a possibility that we might face low levels of recruitment or high levels of dropout. If we are only able to recruit 300 LKDs over 2 years, then we will have 80% power to detect a difference of 15.9% and 90% power to detect a difference of 18.3%. If we are only able to recruit 200 LKDs over 2 years, we will have 80% power to detect a difference of 19.3% and 90% power to detect a difference of 22.1%.

**Table 1 table1:** Power size calculations.

Number of recruited live kidney donors	Control proportion	Intervention proportion (80% power)	Delta (80% power)	Intervention proportion (90% power)	Delta (90% power)
200	0.50	0.693	0.193	0.721	0.221
300	0.50	0.659	0.159	0.683	0.183
400	0.50	0.638	0.138	0.659	0.159

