### Analysis

Research team members at Johns Hopkins will conduct all analyses for this pilot RCT. Descriptive statistical methods will be used to analyze the frequency of key variables, including chi-square and rank-sum tests. Rates of the follow-up compliance among participants in the intervention and control arms will be compared using generalized linear regression. We will perform subgroup analyses for younger donors (age at donation<40 years), older donors (age ≥40 years), men, and women. In addition, the impact of the mKidney system on LKD follow-up compliance will be compared with historical follow-up with a difference-in-difference framework. All analyses will follow an intention-to-treat principle. Data will be analyzed with Stata 15 for Linux (StataCorp Inc).

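### Marking visits after withdrawal as censored does not fit a yes/no submission outcome analysed by intention to treat, and can bias the arm comparison in either direction

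*Protocol article*

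**What the plan says.** All the relevant text is in the Methods of the protocol article.

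- **Outcome (Study Procedure).** The primary outcome is "the rate of policy-defined complete (all components addressed) and timely (60 days before or after the expected visit date) submission of data at all" three visits: 6 months, 1 year and 2 years. It is examined in two ways: "Outcomes will be assessed independently for each follow-up time point and as a composite outcome over the study period".
- **Withdrawal (Study Procedure).** "If participants choose to withdraw, the study team will use the data collected prior to withdrawal and mark the remaining data as censored". The same paragraph adds: "Withdrawal from the RCT would not preclude participants from obtaining regular medical care or follow-up care related to their kidney donation".
- **Model (Analysis).** "Rates of the follow-up compliance among participants in the intervention and control arms will be compared using generalized linear regression". No time-to-event method is named.
- **Principle (Analysis).** "All analyses will follow an intention-to-treat principle". Study Procedure makes the same commitment for the outcomes.

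The Introduction, in its section on the current landscape of donor follow-up, explains that hospitals must gather these data from every donor within a 120-day window around each visit. That duty does not depend on trial participation.

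**The concern.** Censoring belongs to outcomes observed over time, where a participant contributes information up to the moment of leaving. Here the outcome at each visit is a yes or a no, and sending nothing within the window is itself the no. A regression on such an outcome can use a value of 1 or 0. It cannot use a value labelled censored. Unless another rule is written down, the visit becomes missing and the donor leaves both numerator and denominator.

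Two things are at stake. First, the comparison would no longer include all donors as randomised, which is what the plan promises. Second, if the donors who leave differ between arms in number and in how likely they were to submit, the estimated effect of the app is distorted. The Objective section says the trial is meant to supply effect sizes for a larger trial, so a distorted estimate would carry into that trial's sample size.

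The loss is also largely avoidable. The hospital still has to pursue the same data for a withdrawn donor, and donation follow-up care remains open to that donor.

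**Working it through.** **Inputs from the protocol.** 400 donors, 1:1, so about 200 per arm; control compliance 50% (Sample Size and Power Calculation). Significance level and sidedness are not stated.

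**Reproducing the plan's figure.** Table 1 gives a detectable difference of 0.138 at 80% power with 400 donors. With two-sided alpha 0.05, pooled variance under the null and no continuity correction, the mean proportion is 0.569 and

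z = [0.138 - 1.96 × √(2 × 0.569 × 0.431 / 200)] / √[(0.50 × 0.50 + 0.638 × 0.362) / 200] = (0.138 - 0.0971) / 0.0490 = 0.83,

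which gives power of 79.8%. All six cells of Table 1 reproduce in this way, so two-sided 0.05 is used below.

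**Assumptions not in the protocol.** Withdrawal proportions of 0% to 10% per arm; true compliance 50% in both arms (no effect); withdrawers are all non-submitters. The calculation is for one visit after withdrawal. It also applies to the composite for donors who had not missed a visit before withdrawing.

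**Formula.** If a proportion w of an arm is dropped and all of them are non-submitters, the observed rate is 0.50 / (1 - w), on 200 × (1 - w) donors.

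| Withdrawal, app / control | App rate | Control rate | False difference (points) | Chance of a significant result favouring the app |
|---|---|---|---|---|
| 0% / 0% | 50.0% | 50.0% | 0 | 2.5% |
| 5% / 0% | 0.50/0.95 = 52.6% | 50.0% | +2.6 | 7.5% |
| 10% / 0% | 0.50/0.90 = 55.6% | 50.0% | +5.6 | 19% |
| 10% / 10% | 55.6% | 55.6% | 0 | 2.5% |
| 0% / 10% | 50.0% | 55.6% | -5.6 | 0.1% |

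The last column uses the normal approximation for two proportions. For 10%/0%, the pooled rate is 200/380 = 0.526, the null standard error 0.0513 and the alternative standard error 0.0512, so z = (0.0556 - 1.96 × 0.0513) / 0.0512 = -0.88 and the probability is 19%. Simulation with 200,000 runs agrees.

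**Equal withdrawal with a true effect.** With 10% in each arm, a true difference of 13.8 points becomes 0.138 / 0.90 = 15.3 points.

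**If withdrawers are not all non-submitters.** Take 10%/0% and let withdrawers submit at rate s. The observed app rate is (0.50 - 0.10 × s) / 0.90.

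| s | App rate | False difference (points) |
|---|---|---|
| 0 | 55.6% | +5.6 |
| 0.25 | 52.8% | +2.8 |
| 0.50 | 50.0% | 0 |
| 0.75 | 47.2% | -2.8 |
| 1 | 44.4% | -5.6 |

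**Keeping all donors.** When withdrawers really are non-submitters and are counted as such, the simulated difference is zero and the two-sided error stays at about 5% in every withdrawal pattern tried.

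**The case against.** The strongest reply is that censored may be only a data-status label. The sentence does not say that such visits leave the denominator, the plan commits to intention to treat, and a separate analysis plan, not shown here, may say how these visits are handled. This stands in part: removal is the natural reading, not an explicit statement. But the article does state a rule, and that rule as worded cannot be carried out in the named model while every randomised donor stays in the analysis.

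A second reply is that the rule reaches few people. It covers only donors who formally leave the trial. A donor who ignores the prompts or stops opening the app has not withdrawn, is not censored, and still counts as a non-submitter. A donor who missed a visit before withdrawing has already failed the composite. Both points are right and limit the likely size.

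A third reply is that withdrawers may well submit. Hospital staff may still contact them, so a withdrawn app-arm donor may return to something like standard care, where the protocol assumes 50% compliance. At that rate the bias is zero. This also stands.

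A reader might go further and infer that the rule will create a false benefit of the app, because only that arm has something burdensome to leave. The documents do not support this. They give no withdrawal data for either arm, and in an open-label trial control donors may leave too.

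A reader might also fault the power section for treating dropout as lost sample size, since it says: "There is a possibility that we might face low levels of recruitment or high levels of dropout". The scenarios that follow, and the first column of Table 1, are expressed as numbers recruited, so that criticism does not hold.

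**Conclusion.** The point holds as a conflict between the withdrawal rule and the promised analysis. A censored value cannot enter a regression on yes/no submission, so on the natural reading formally withdrawn donors disappear from later visits and, unless already failed, from the composite. The conflict with intention to treat exists whichever way any bias runs.

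The size cannot be established from the documents. Under the assumed scenarios the distortion runs from -5.6 to +5.6 points, set against a planned detectable difference of 13.8 points. It is zero when withdrawers would have submitted at the common 50% rate. Equal withdrawal creates no false difference under the null, but overstates both rates and enlarges a true effect. The positive figures need more withdrawal in the app arm by donors less likely to submit. They show what the rule permits and are not a forecast.

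The wording should be settled before outcome data are analysed, because it governs the primary outcome in a trial where the analysts know the allocation.

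**What to change.** Replace the censoring sentence with a rule along these lines:

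- All randomised donors stay in the denominator at every visit and in the composite.
- For a donor who withdraws from study procedures, the outcome is taken from the hospital's routine OPTN follow-up record where consent permits.
- A visit with no complete, timely record counts as not compliant.
- Where consent to use the record is withdrawn, the visit counts as not compliant in the primary analysis. A sensitivity analysis varies those outcomes in both directions and separately by arm.

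The sensitivity analysis is needed because counting unknown outcomes as failures is itself an assumption. If 10% of the app arm refused record use and would have submitted at 50%, the app rate would read 0.50 - 0.10 × 0.50 = 45%, a false -5 points.

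The cost is a short change of text, possibly one consent line allowing use of routine records after withdrawal, and one small extra analysis. No additional visits or data collection from donors are required. If a separate analysis plan already contains such a rule, the protocol sentence should be brought into line with it.
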